##### Conceptual model and evaluation of the proposed mechanism of action

According to the deliberate practice model, both repetition and specific, performance-based feedback are crucial to improving provider skill [72–75]. LyssnCBT is designed to enhance exposure to repeated practice opportunities (i.e., CBT sessions) with exactly the type of specific, performance-based feedback emphasized in the deliberate practice model. In support of this, high-quality implementation efforts that are inclusive of practice with feedback increase CBT competence [49]. The skills training involved in CBT (encompassing both cognitive interventions like generating alternative explanations and cognitive coping skills, and behavioral interventions, like behavioral activation and coping skills) act as mediators in reducing distress and impairment among individuals with mental health problems. Adopting principles of experimental therapeutics outlined in the NIMH strategic plan [76] and applying them to the conceptual frameworks guiding LyssnCBT, the following mechanism of action will be assessed: LyssnCBT will provide performance-based feedback on CBT fidelity, which should improve therapist CBT skills which in turn should improve client outcomes. Importantly, most process or mechanism research has been limited to 100–200 sessions due to human-based observational coding [77]. In the present study, the proposed mediation model above will be assessed using more than 18,000 sessions.

The hypothesized mediation model will be tested using mixed models [78]. Specifically, analyses will test the total effect (or “c” pathway in mediation literature) of LyssnCBT on client outcomes (i.e., PHQ-9, GAD-7, premature drop-out), then the effect of LyssnCBT on CTRS scores (or “a” pathway). Finally, analyses will test the direct effect of LyssnCBT on client outcomes (“c prime”) while controlling for the effect of the CTRS mediator (“b” pathway). The indirect (“a*b”) effect will be tested via bootstrap confidence intervals [79] and is a direct estimate of the hypothesized mechanism. Two additional analyses are also planned. While the above analyses provide the traditional approach to mediation, it is specifically hypothesized that it is *changes* in CBT fidelity (i.e., CTRS scores) due to LyssnCBT which would drive improved client outcomes. To examine this hypothesis, CTRS deviation scores will be created. Mean CTRS scores during SAU will be estimated for each therapist and for each CTRS item (i.e., mean *Agenda* score during SAU phase). These means will be subtracted from each corresponding CTRS score during the LyssnCBT phase (e.g., if mean *Agenda* during SAU is 2.5 and 6 in a new session, the deviation score would be + 3.5). These CTRS deviation scores will provide somewhat more specific information on whether the improvement in CBT fidelity is driving client outcomes. Finally, the Lyssn platform collects user-interaction data, which will be used to examine whether time spent reviewing sessions and interacting with the LyssnCBT UI are predictive of improved client outcomes.

##### Power and sample size

Power and sample size estimation took into account a number of factors: 1) correlation of CBT fidelity and client symptoms within therapists, 2) repeated measures, 3) stepped wedge design, and 4) a range of possible effect-sizes. Intraclass correlation coefficients (ICC; i.e. the correlation in the data due to nesting) were based on recent analyses of more than 400 CBT therapists and associated CBT fidelity ratings (ICC = 0.20; [80]) and published literature on patient symptoms (ICC = 0.10; [14]). Power and sample size focused on the effect of LyssnCBT on client outcomes, where a smaller effect size is expected as compared to therapist CBT skill, which is being directly targeted by LyssnCBT. Sample size was estimated using the formula for mixed model power analysis developed by Raudenbush and colleagues [81] that incorporates therapist ICCs and repeated measures, used in conjunction with a design effect from the specific stepped-wedge design proposed [66]. Because stepped-wedge studies include both within and between therapist comparisons, they typically have greater power than similar parallel groups cluster randomized trials [82]. A range of effect sizes for LyssnCBT on client outcomes (from 0.05 to 0.25) and therapist sample sizes were examined. Given the proposed design of 5 clinics, 50 providers, 1,875 total clients, and 18,750 repeated measures, the current design has power of 0.80 or more to detect LyssnCBT effects of *d* = 0.15 or greater. This would represent a ‘small’ effect, but given the number of clients who receive CBT services in a given year, this would still entail a large effect in the population over time [83].

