LyssnCBT will be compared to SAU using a stepped-wedge design in which each clinic will have SAU and LyssnCBT phases. Stepped wedge designs allow the intervention (here, LyssnCBT) to eventually roll out to all clinics and therapists and also has greater power than a parallel cluster randomized trial [63]. As shown in Fig. 2, all 5 clinics will start with SAU (black solid lines), and clinics will be randomized to begin LyssnCBT sequentially over time (dashed purple) using simple randomization. The names of the five participating agencies will each be enclosed in individual sealed envelopes, and every two months, a study team member will select one envelope with the name of the agency to begin LyssnCBT. At the start of the trial when all clinics are in the SAU phase, all clinics will begin using a modified version of the Lyssn platform for recording sessions that provides access to the recording and session sharing functionality, but no other features (e.g., speech-to-text transcription, annotation tools, any AI-generated metrics). When a clinic is randomly selected to use LyssnCBT, there will be an onboarding and training session to cover the software and clinical / supervision protocols. Participants may withdraw or take away permission to use and disclose their information at any time by sending written notice to the investigator for the study. If they withdraw their permission, they will not be able to stay in the study.

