#### Data analysis plan

CBT fidelity, client symptom measures (PHQ-9, GAD-7), and client drop-out will be analyzed with mixed-effects models (also called hierarchical or multilevel models; [67–70]). Mixed models are very flexible with respect to nested and imbalanced data, where the current data will contain repeated measures within clients and within therapists with varying numbers of sessions and clients. Within each individual clinic, a stepped wedge design is similar to an interrupted time series, with pre-intervention (i.e., SAU) and post-intervention (i.e., LyssnCBT) phases. To model the intervention effect, separate slopes will be examined for time by phase to capture differential changes in outcomes across the two phases. *Condition* (LyssnCBT vs SAU) will be dummy-coded, and clinics will also be included in the model as dummy-coded control variables. Analyses across the outcomes will be very similar, with the exception that client drop-out is a binary outcome, whereas a logistic mixed effects model will be used instead. The primary focus in all analyses is the main effect of *Condition* and its interaction with *Time* (during the phase since LyssnCBT started). Finally, sensitivity analyses will examine missing data. Missing data could be a function of a therapist not recording a session, or of a client not completing self-report measures. The research team will review weekly reports of anticipated recordings and assessments to prevent missing data whenever possible. No significant challenges with missing data are anticipated, though calculations have assumed 20% attrition in power analyses (see below). Mixed-effects models provide unbiased estimates in the presence of missing data as long as missing data can be assumed Missing at Random (MAR; [70]). If missing data is greater than 20% or there are other concerns about the MAR assumption, a pattern-mixture approach will be used to (potentially) non-ignorable missing data [71].

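### Power of 0.80 at d = 0.15 is not supported for five randomised clinics, because neither the power inputs nor the analysis model carries clinic-by-time variation

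*Protocol article*

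**What the plan says.** The randomised unit is the clinic. Under Phase 2 research design and methods, "clinics will be randomized to begin LyssnCBT sequentially over time (dashed purple) using simple randomization". The mechanism is five envelopes, one per agency, and "every two months, a study team member will select one envelope with the name of the agency to begin LyssnCBT". All participating therapists and clients in a clinic therefore switch together.

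The Power and sample size section works one level down. The clustering it lists is "correlation of CBT fidelity and client symptoms within therapists", with ICCs of 0.20 for fidelity and 0.10 for symptoms. The formula is one "that incorporates therapist ICCs and repeated measures, used in conjunction with a design effect from the specific stepped-wedge design proposed". With a threshold of d = 0.15, and a sample of 5 clinics, 50 therapists, 1,875 clients and 18,750 measurements, the section concludes that "the current design has power of 0.80 or more to detect LyssnCBT effects of" that size and above. The section gives no correlation at clinic or clinic-by-period level.

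The Data analysis plan describes data nested in clients and therapists, with time slopes that differ by phase, and says that "clinics will also be included in the model as dummy-coded control variables". It also says that the power calculations assumed 20% attrition.

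**The concern.** With one clinic switching per step, anything that shifts a whole clinic at a particular time competes directly with the intervention effect. The article gives reasons to expect such shifts. It foresees provider turnover and the possible addition of providers or sites (Potential problems and alternative strategies), and it has each program build the tool into its own intake and supervision. A clinic dummy takes out the clinic's average level, not its movement over 18 months. A therapist random effect does not take it out either, because the movement is shared by all therapists in the clinic.

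If that variance exists and is left out, the 50 therapists are treated as more independent than they are. The standard error of the Condition effect is then too small and the power figure too high. At stake are the p-values for symptoms and fidelity, and the claim that a small effect is detectable.

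**Working it through.** **Inputs from the protocol article.** 5 clinics, 50 therapists (10 per clinic on average), 1,875 clients, 10 sessions per client, symptom ICC 0.10, a step every 2 months, 18 months of data, 20% attrition.

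**Assumptions not in the article.** Two-sided alpha 0.05; within-client correlation r = 0.5; six periods (one baseline plus five steps) or nine (18/2); clinic-by-period variance s of 0, 0.5, 1 or 2% of total variance, constant within a period; normal approximation. Effects are in units of the total standard deviation.

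**Step 1: the stated figure.** Take therapists as clusters and use the standard closed-form stepped-wedge design effect with k = 5 steps, one baseline period and n clients per therapist per period:

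DE = [1 + ρ(kn + n − 1)] / [1 + ρ(kn/2 + n − 1)] × 3(1 − ρ) / [2(k − 1/k)]

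The variance of a 10-session client mean is r + (1 − r)/10 = 0.55 of that of a single score.

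- No attrition: n = 1,875/(50 × 6) = 6.25. DE = (4.65/3.0875) × (2.7/9.6) = 0.4236. Effective N = 1,875/(6 × 0.4236 × 0.55) = 1,341. SE = 2/√1,341 = 0.0546. Power = Φ(0.15/0.0546 − 1.96) = 0.78.
- 20% attrition: n = 5, DE = 0.4139, effective N = 1,500/(6 × 0.4139 × 0.55) = 1,098, SE = 0.0604, power 0.70.

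With attrition, 0.80 is reached at r of about 0.37; at r = 0.6 power is 0.64. So a figure near 0.80 can be obtained with therapist-only clustering and favourable inputs. It cannot be confirmed, because alpha, r and the form of the design effect are not given.

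**Step 2: type I error if clinic-by-period variance is omitted.** Now use the stated structure: clinic dummies, a therapist random effect, and therapist-by-period means with error variance v = 0.9 × 0.55/m = 0.495/m, where m is clients per therapist per period. With 10 therapists per clinic, the true variance of the Condition estimate exceeds the model's by the factor R² = 1 + 10s/v, and type I error is 2[1 − Φ(1.96/R)].

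| Periods, attrition | m | v | s = 0.5% | s = 1% | s = 2% |
|---|---|---|---|---|---|
| 6, none | 6.25 | 0.0792 | 12.5% | 19.3% | 29.7% |
| 6, 20% | 5.00 | 0.0990 | 11.0% | 16.7% | 25.9% |
| 9, none | 4.17 | 0.1188 | 10.0% | 14.9% | 23.2% |
| 9, 20% | 3.33 | 0.1485 | 9.0% | 13.0% | 20.1% |

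Example (6 periods, no attrition, s = 1%): R² = 1 + 0.10/0.0792 = 2.263, R = 1.504, 1.96/1.504 = 1.303, type I error 19.3%. At s = 0, R = 1 and the error is 5%.

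**Step 3: power at d = 0.15 with the variance included.** Generalised least squares on the same means gives the SE at s = 0. Multiplying by R gives the SE at other values. Power = Φ(0.15/SE − 1.96). Each cell shows no attrition / 20% attrition.

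| Model | SE at s = 0 | s = 0 | 0.5% | 1% | 2% |
|---|---|---|---|---|---|
| 6 periods, linear or categorical time | 0.0583 / 0.0651 | 0.73 / 0.63 | 0.52 / 0.47 | 0.40 / 0.37 | 0.28 / 0.26 |
| 9 periods, linear time | 0.0578 / 0.0646 | 0.74 / 0.64 | 0.59 / 0.52 | 0.48 / 0.43 | 0.35 / 0.33 |
| 9 periods, categorical time | 0.0641 / 0.0717 | 0.65 / 0.55 | 0.50 / 0.44 | 0.41 / 0.37 | 0.30 / 0.28 |
| 6 periods, no time term | 0.0368 / 0.0412 | 0.98 / 0.95 | 0.89 / 0.84 | 0.77 / 0.73 | 0.58 / 0.55 |
| 9 periods, no time term | 0.0366 / 0.0409 | 0.98 / 0.96 | 0.93 / 0.89 | 0.86 / 0.81 | 0.71 / 0.67 |

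With a time trend and s = 1%, the effect detectable with 80% power (2.80 × SE) is d = 0.22 to 0.26.

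**The case against.** **The clinic is not ignored.** The dummies absorb all constant differences between clinics, and Step 2 shows an error rate of exactly 5% when there is no clinic-by-time variance. This stands. A reader might infer that type I error is inflated and the intervals will be too narrow. The article does not support that as fact, because it gives neither clinic-by-time variance nor between-clinic variation in the effect. The risk is conditional on at least one being above zero.

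**Detail may sit elsewhere.** This is a journal article, the analysis plan is not shown, and the cluster level of the cited design effect cannot be checked. The description of nesting need not list every random effect. This stands in part: the absence of a small-sample method is no finding, and it would be wrong to say that the plan uses large-sample normal inference, since no reference distribution is named. The power claim is different. It is a definite figure, and every correlation named in its support is at therapist level or below.

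**The size can be overstated.** A reader might reason that five clinics leave 4 degrees of freedom and that power collapses. The article does not imply this. A model with a clinic-by-period term leaves about 30 − 5 − 5 − 1 = 19 residual degrees of freedom with six periods, or 45 − 5 − 8 − 1 = 31 with nine. Likewise, a working model with an SE near 0.033 would show much larger inflation, but with a time trend fitted, as planned, it would also imply power above 99% at d = 0.15 (0.15/0.033 − 1.96 = 2.59). An SE of 0.0535 corresponds to power of exactly 0.80.

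**Without a time trend the claim roughly survives.** At 1% variance, power is 0.73–0.86. But the article plans time slopes by phase, and the type I error in Step 2 does not depend on whether time is fitted.

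**Conclusion.** The point holds in a limited form. Clinics are randomised, but clinic-by-time variation appears in neither the stated power inputs nor the stated model. The figure of 0.80 or more at d = 0.15 is unsupported for the design as randomised. With time fitted, power is about 0.55–0.74 at zero clinic-by-period variance, 0.44–0.59 at 0.5% and 0.37–0.48 at 1%. Type I error is at risk, not shown to be inflated: 5% at zero, and about 9–13%, 13–19% and 20–30% at 0.5, 1 and 2% if the term is omitted.

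All these sizes rest on assumed values for the clinic-by-period variance, a period-constant clinic effect, r = 0.5, alpha 0.05 and 0–20% attrition. A different form of drift or a different r would move them. The power figures use a normal approximation, so a small-sample reference distribution would lower them somewhat.

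**What to change.** Add a clinic-by-period random effect to the primary models, with Kenward-Roger small-sample inference where the model allows it. Alternatively, or as a check, use a randomisation test over the 5! = 120 possible clinic orders (smallest two-sided p about 2/120 = 0.017). Restate the power over clinic-by-period variances of 0, 0.5, 1 and 2% of total, with the 20% attrition and the planned time terms included and with alpha, the within-client correlation and the level of the design effect written out. Do not claim 0.80 at d = 0.15 without that qualification.

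The cost is some wording, one variance term, one permutation run, wider intervals and a less favourable power statement. None of this needs extra participants, but it does not restore the power: if clinic-by-period variance is near 1%, the trial is sized for effects nearer 0.22–0.26, and the report should say so.

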## Data management

All data will be recorded using a secure, password protected, HIPAA compliant cloud platform (LyssnCBT). The platform will be hosted on Amazon Web Services (AWS) and require two-factor authentication to ensure the security of all sensitive patient data. Lyssn maintains a Business Associate Agreement (BAA) with AWS to ensure that both parties are adhering to HIPAA guidelines. This platform streams data directly to secure data storage, ensuring that recordings do not reside on less secure therapist computers or tablets. All hard disks utilize full hard drive encryption (in compliance with HIPAA guidelines) and client identifiers have a second level of encryption in the database tables. This cloud-based recording system has already been built and has been used to securely record and store sessions as part of R44 DA046243. Once files have been recorded, they are then processed on the cloud-based platform. This processing includes speech signal processing methods, voice activity detection, speaker segmentation (or diarization), and automated speech recognition (ASR). LyssnCBT therapist competence ratings and speech feature data will then be used in the computer-generated summary reports. These summary reports will be viewable on the same secure, HIPAA compliant cloud platform used for recording. Therapists and supervisors will view the LyssnCBT feedback reports together during supervision, and therapists may also choose to log in to view feedback metrics independently. All other data and source materials are only accessible to the researchers.

The research team will only have access to individually identifiable private information (e.g., name and contact information) on an as-needed basis, such as to confirm that recordings are only being copied for sessions from consented therapists and that LyssnCBT feedback reports are given to the appropriate therapist only.

Data transfer of all files will be protected using strong Advanced Encryption Standard (AES) encryption; electronic data will only be maintained on network servers and computers that incorporate security protections; any hard copies that contain identifiable data will storedin locked file cabinets; subject-identifiable information will be replaced with identification numbers at the earliest possible time; and subject-identifiable information and the link to identification numbers will be kept separately from data.

## Discussion

Artificial intelligence holds great promise for advancing our ability to evaluate therapist skills at scale, providing a view inside the black box of psychotherapy as it is delivered in routine care. This study will employ user-centered design to engage community stakeholders in refining a tool to evaluate and support clinicians’ CBT skills, and then evaluate the impact of that tool on CBT skill and client outcomes in a publicly funded mental health care system. The study will also examine the hypothesized mechanism by which LyssnCBT affects clinician and client outcomes. It will be among the first studies to test artificial-intelligence generated metrics and tools to improve skills and client outcomes in routine mental health care. Outcomes will have a significant impact on the advancement of strategies to implement mental health EBPs at scale and with fidelity, which in turn may have positive impacts for broader accessibility of these treatments. Trial results will be reported in peer-reviewed publications, at scientific presentations, and through open presentations to the community mental health system within which this research will be conducted.

### Potential problems and alternative strategies

It is possible that technology problems (e.g., lack of computer or computer access) will require a more extensive period of system enhancements. The study team has extensive past history working within DBHIDS and similar sites, and the pilot data suggests that sites have the necessary, basic technology infrastructure. However, the investigators will be attentive to these technical issues during the Phase 1 research and have budgeted for just this possibility. Provider turnover and client no-shows could affect the retention rate in the randomized trial and/or increase missing data, reducing statistical power and increasing standard error. Additionally, recruitment for the randomized trial may be slower than expected. The team will proactively employ several strategies to mitigate this risk. If the study flow does not support the recruitment targets by the end of month 9 of Phase 2, the team will work with the recruited agencies and DBHIDS leadership to either identify new providers for recruitment at existing study sites or expand recruitment effort to additional sites.

### Potential for impact

The DBHIDS network includes over 300 agencies. Conservatively assuming that each agency has 10 therapists and each therapist sees 30 clients per week, that is 90,000 sessions per week, approximately 4.5 million per year – in *one* publicly-funded behavioral health system in a single large American city. There are currently no feasible methods for estimating the quality of even a fraction of those sessions. The current research builds upon a robust, existing platform and lays the groundwork for a feasible, technology-enabled assessment of CBT intervention quality at scale, which can inform performance-based feedback for training, supervision, and quality assurance. The combination of the team, the project, and the partnership with DBHIDS presents a unique opportunity to massively scale up quality monitoring of CBT interventions, and the underlying methodologies would lay a foundation for psychosocial intervention quality monitoring and feedback in general. The implications of this research would be improved outcomes for clients, improved support for therapists, and improved quality assurance processes for behavioral healthcare systems.

## Data Availability

Not applicable.

## Abbreviations

AI: Artificial Intelligence
AIM: Acceptability Intervention Measure
BCI: Beck Community Initiative
CBT: Cognitive Behavioral Therapy
CMH: Community Mental Health
CTRS: Cognitive Therapy Rating Scale
DBHIDS: Department of Behavioral Health and Intellectual disAbility Services
EBPs: Evidence-Based Psychotherapies
FIM: Feasibility of Intervention Measure
GAD-7: Generalized Anxiety Disorder 7
IAM: Intervention Appropriateness Measure
ICC: Intraclass Correlation
IT: Information technology
MAR: Missing at Random
MI: Motivational Interviewing
ML: Machine learning
PHQ-9: Patient Health Questionnaire 9
SAU: Services as Usual
SP: Standardized patient
UCD: User-Centered Design
UI: User Interface
